### Study schedule

Table 1 summarises the study schedule.

**Table 1 T1:** Study schedule

Time point	**Screening** < 2 weeks	**Baseline** Day 0	**Visit 3** Month 1^1^	**Visit 4** Month 3^2^	**Visit 5** Month 6	**Visit 6** Month 9	**Visit 7** Month 12^2^
Informed consent	X						
Record demographics & handedness	X						
Review inclusion/exclusion criteria	X	X					
Review medical history	X	X					
Details of stroke	X						
Pre stroke function (inc Oxford Handicap Scale^)^)	X						
Abbreviated Mental Test Score (AMTS)	X						
Sheffield Aphasia Screening Test	X						
Action Research Arm Test (ARAT)	X	X	X	X			X
Motricity Index		X	X	X			X
Grip strength		X	X	X			X
Nine Hole Peg Test		X	X	X			X
Modified Ashworth Scale	X	X	X	X			X
Self rating of severity		X	X	X			X
Upper limb pain (numerical rating scale)^3^		X	X	X			X
Patient selects upper limb goals		X					
Review upper limb goal attainment			X				
Barthel ADL Index^3^	X		X^3^	X^3^			X^3^
Quality of life – Stroke Impact Scale^3^	X		X^3^	X^3^			X^3^
Quality of life – Euroquol-5D^3^	X		X^3^	X^3^			X^3^
Resource utilisation questions^3^	X		X^3^	X^3^			X^3^
Pregnancy test^4^		X		X^6^	X^6^	X^6^	
Randomisation		X					
Treatment with Dysport^5^		X		X^7^	X^7^	X^7^	
Commencement of 4 week upper limb therapy programme		X		X^7^	X^7^	X^7^	
Clinical assessment by study therapist		X		X	X	X	X
Concomitant medications (inc anti-spasticity treatment)	X	X	X	X			X
Adverse Events		X	X	X			X
Participants views and experience			X				X

1. Visit window is +3 days.

2. Visit window is +5 days.

3. Questionnaires will be sent to the participant for completion 1 week prior to the visit. Participants will bring completed forms to the visit.

4. For female participants at risk of pregnancy.

5. Participants in the intervention group only.

6. Pregnancy test to be performed prior to any additional botulinum toxin injections.

7. Additional botulinum toxin injections/upper limb therapy to be provided if clinically appropriate

### Statistical analysis

The primary endpoint is the ARAT[20] score at 1 month. The analysis will be undertaken on an "intention to treat" basis; participants will analysed in the group to which they were randomised.

For each participant it will be determined if there has been a significant improvement in function based on the change in ARAT score. A successful outcome will be defined as:

(i) a change of 3 or more points on the ARAT scale for a participant whose baseline ARAT score is between 0 and 3

(ii) a change of 6 or more points on the ARAT scale for a participant whose baseline ARAT score is between 4 and 51

(iii) a final ARAT score of 57 for a participant whose baseline ARAT score is 52 or greater.

The proportion of "successes" in each group will then be compared using Fisher's exact test. An interval estimate of the relative odds of a successful outcome in each group will also be calculated. This interval estimate of effect size will be taken forward into the economic evaluation.

Secondary outcomes will also be analysed on an "intention to treat" basis. A test appropriate to the type of variable will be undertaken.

A pre-specified sub group analysis will consider the effect of time since stroke as a covariate. It is hypothesised that participants who have recently had a stroke will have a better response to treatment than those who had a stroke some time ago.

The power calculation used prognosis based methodology[59]. A clinically important treatment effect is defined as a difference in good outcomes between intervention and control groups of 15% where a good outcome is defined above for each of the ARAT group; it is expected to see 20% of the control group achieve good outcomes and 35% of the intervention group achieve good outcomes. Using Fleiss' method[60] for a binary outcome and inflating the sample size by 10% to allow for attrition we need to recruit a total sample of 332 participants to give us 80% power to detect a 15% difference in good outcomes assuming a two-tailed test and a significance level of 5%. We are aiming to recruit 50% of the sample from the ARAT 0–3 group and 50% from the ARAT 4–56 group.

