### Randomisation

Randomisation is by a central independent web based randomisation service from the Clinical Trials Unit, Newcastle University. Participants are stratified according to level of upper limb function (ARAT 0–3, ARAT 4–28, ARAT 29–56) and randomised to intervention or control in a 1:1 ratio.

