#### (4) Inclusion criteria

Prospective studies of upper limb recovery have shown that baseline impairment is a strong predictor of outcome. To demonstrate whether botulinum toxin plus upper limb therapy can improve arm function (primary outcome), it was initially thought important to exclude those participants with no retained upper limb function (ARAT 0–3). Due to initial low recruitment, this was later reconsidered and it was decided that it would be valuable to include stroke patients with all levels of reduced upper limb function (ARAT 0–56).

The study also initially excluded participants with cognitive impairment or significant speech problems measured by the Abbreviated Mental Test Score and Sheffield Aphasia Screening Test. This was felt to be too restrictive, excluding patients who were keen to participate. This inclusion criteria was relaxed to include all participants capable of performing the ARAT and complying with the upper limb therapy programme.

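### The primary Fisher's exact test ignores the ARAT randomisation strata: it is valid and has the stated 80% power, but gives up about 3 points of power against a stratified test, and more if the strata are prognostic.

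*Protocol article*

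**What the plan says.** Under Randomisation, the protocol article states: "Participants are stratified according to level of upper limb function (ARAT 0–3, ARAT 4–28, ARAT 29–56"), with 1:1 allocation. Under Statistical analysis, success at one month depends on baseline ARAT: a gain of at least 3 points from a baseline of 0–3, a gain of at least 6 from 4–51, or a final score of 57 from 52 or above. The proportions of successes "in each group will then be compared using Fisher's exact test", and an interval for the relative odds is to be calculated and passed to the economic evaluation. Neither stratum nor baseline score is named in this comparison. Time since stroke is the only covariate mentioned, and that is for a subgroup analysis.

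In the list of amendments, item (4) Inclusion criteria reports that prospective studies of upper limb recovery show that "baseline impairment is a strong predictor of outcome".

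For the sample size, "it is expected to see 20% of the control group achieve good outcomes and 35% of the intervention group achieve good outcomes". The calculation is described as "Using Fleiss' method[60] for a binary outcome", inflated by 10% for attrition to 332 in total, "to give us 80% power to detect a 15% difference in good outcomes", "assuming a two-tailed test and a significance level of 5" per cent. Half of the sample is to come from ARAT 0–3 and half from ARAT 4–56.

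**The concern.** Stratified randomisation balances the arms within each ARAT band. If the bands differ in their chance of success, the treatment contrast varies less from trial to trial than under simple randomisation. A single pooled 2×2 table does not credit that reduction, so the test runs below its nominal level. Fisher's exact test is conservative even before this. The plan therefore stratifies on a factor that it regards as prognostic and then does not use the stratification in the analysis. What is at stake is efficiency on the primary endpoint, in a trial whose amendments repeatedly cite low recruitment.

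**Working it through.** **1. Reproduce the sample size.** Inputs from Statistical analysis: p₁ = 0.20, p₂ = 0.35, two-sided 5% (z = 1.96), 80% power (z = 0.842), mean rate 0.275.

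- Uncorrected: n₀ = [1.96√(2 × 0.275 × 0.725) + 0.842√(0.16 + 0.2275)]² / 0.15² ≈ 138 per arm.
- With Fleiss' continuity correction: n = (n₀/4)[1 + √(1 + 4/(n₀ × 0.15))]² ≈ 151 per arm, or 302 in total.
- Attrition: 302 × 1.10 = 332.2, which matches the stated 332. The uncorrected figure (276 in total) gives only 304 to 307.

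So 332 is the continuity-corrected figure, and that correction approximates Fisher's test.

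**2. Exact behaviour of the planned test.** With 332 less 10%, about 149 per arm are evaluable. Full enumeration of the two binomials gives:

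| Test | Power, 20% v 35% | True size at 20% null |
|---|---|---|
| Fisher's exact | 79.9% | 3.6% |
| Pearson, uncorrected | 83.2% | 5.0% |

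Fisher's conservatism alone costs 83.2 − 79.9 = 3.3 points. This part rests only on the article's own figures.

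**3. Adding the strata.** The article gives no success rates by stratum, so those below are assumptions. Simulation used 150 per arm, 75 in each of two strata (ARAT 0–3 / ARAT 4–56), with overall rates of 20% and 35%. CMH is without continuity correction.

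| Control v intervention, by stratum | Fisher | CMH | Gain (points) |
|---|---|---|---|
| 20/20 v 35/35 | 80.2% | 83.5% | 3.3 |
| 10/30 v 25/45 | 80.8% | 85.3% | 4.5 |
| 5/35 v 20/50 | 81.7% | 88.0% | 6.3 |
| 5/35 v 15/55 | 82.1% | 89.2% | 7.1 |

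A second simulation used 149 per arm, all three bands (75/50/24 per arm) and a common odds ratio. It gave gains of 3.2 points with equal strata, 5.2 at 10%/30% and 7.7 at 5%/35%. Fisher's true size fell to 3.1% at 10%/30% and 2.3% at 5%/35%, while CMH stayed between 4.8% and 5.1%. With a continuity correction, the gain of CMH shrank to about 0, 1.9 and 5.0 points in the same three cases.

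**4. Effect on intervals** (150 per arm, two equal strata).

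- *Odds ratio.* Pooled SE of the log odds ratio = √[1/(150 × 0.2 × 0.8) + 1/(150 × 0.35 × 0.65)] = 0.266. The stratum-adjusted SE (inverse-variance) is 0.276, 0.293 and 0.295 in the three unequal scenarios, so it rises.
- *Risk difference.* Pooled SE = √[(0.16 + 0.2275)/150] = 0.0508. The stratified SE is √{Σ 0.25[p_c(1−p_c) + p_t(1−p_t)]/75}. At 10/30 v 25/45 this is √(0.25 × 0.735/75) = 0.0495. At 5/35 v 20/50 it is √(0.25 × 0.685/75) = 0.0478. At 5/35 v 15/55 it is √(0.25 × 0.65/75) = 0.0465. These are about 3%, 6% and 8% smaller than the pooled value.

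**The case against.** The strongest reply is that test and sample size match. The calculation already paid for Fisher's conservatism, so the plan does what it promises and controls type I error. That stands: a reader might infer that the trial is underpowered, and step 2 shows that it is not. The loss is relative to a better test, not to the plan.

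Second, a reader might attribute the whole loss to ignoring the strata. The documents do not support that. About 3 points come from Fisher against an uncorrected test. Anything beyond depends on stratum rates that the article does not give. Its statement on baseline impairment concerns recovery, not the dichotomised success. The lower threshold for ARAT 0–3 was set because those participants were expected to improve less (amendment item (6) Statistical analysis), and it may bring success rates closer together. Baseline ARAT thus enters the outcome definition, though not the test. This also stands, and it is why the larger gains are conditional.

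Third, a reader might infer that the planned interval is too wide. For the relative odds that is wrong: the log-scale SE rises with adjustment when the strata are prognostic. Power improves because the conditional odds ratio lies further from 1. Only a risk difference becomes more precise.

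Finally, follow-up had ended in June 2008 (Current study status) and the primary analysis had already been revised once. Another change of test is not trivial, so timing has to govern the remedy.

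**Conclusion.** The point holds as a matter of efficiency. The primary test is valid, meets the stated 80% power and is conservative, with a true size of about 3.6% at a 20% null rate and lower if the strata are prognostic. Against CMH without continuity correction it gives up about 3 points with equal stratum rates. It gives up about 4 to 7 points if control rates range from 10%/30% to 5%/35% across strata, or slightly more (7.7) at 5%/35% in the three-band simulation with a common odds ratio. These gains assume a roughly even split between ARAT 0–3 and 4–56, 149 to 150 evaluable per arm, and no continuity correction.

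The same criticism should not be extended to the secondary outcomes. The article says only that "A test appropriate to the type of variable will be undertaken", which neither fixes nor excludes baseline adjustment. That detail commonly belongs to an analysis plan, and none is shown.

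**What to change.** Before any unblinded comparison, make the primary test a CMH test without continuity correction, stratified by the three ARAT randomisation bands, or a logistic model with ARAT stratum. Keep Fisher's exact test as a sensitivity analysis.

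Report the stratum-adjusted risk difference with its 95% CI alongside the planned odds-ratio interval. State that a stratum-adjusted odds ratio is a conditional measure whose interval need not be narrower, and say which odds-ratio interval goes into the economic evaluation.

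If unblinded comparison has already happened, leave Fisher's test as primary and report the stratified analysis as a labelled supplementary analysis.

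The change needs no new data and no change in sample size. Because data collection is complete, it does need a dated, documented amendment made without knowledge of results by group.

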### Randomised controlled trials of botulinum toxin in the treatment of upper limb spasticity following stroke

After injection botulinum toxin causes local paresis of muscles as a result of blocking cholinergic transmission at the neuromuscular junction. The clinical treatment effect lasts for 3–4 months[6]. To date, nine randomised controlled trials have evaluated its use for the treatment of upper limb spasticity following stroke [7-15], and three systematic reviews have been published [16-18] (two trials[14,15] and two systematic reviews were published following the start of this study[17,18]).

Trials have reported a measurable reduction in resistance to passive movement on the Modified Ashworth Scale within 6 weeks, which then reduces towards 12–16 weeks, often losing statistical significance at this time. The main benefits of spasticity reduction appear to be in terms of global patient/physician ratings and itemised passive disability scores (notably hand hygiene). Only one study (published after this study commenced) has reported an improvement in active upper limb function[15].

As the treatment effect of botulinum toxin lasts only 3–4 months, injections need to be repeated to offer sustained benefit. Only one trial (published after this study commenced) has considered the impact of repeat injections[14]. This has provided limited evidence to support continued use of botulinum toxin for spasticity reduction.

Guidelines for the use of botulinum toxin in the treatment of spasticity recommend that it should be used in combination with a rehabilitation programme[6], but no trial to date has attempted to standardise upper limb therapy. No study has looked at the cost-effectiveness of treatment. Although transient muscle weakness at higher doses of botulinum toxin is well recognised, studies reported no unexpected adverse events, however, the event reporting system was often unclear.

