### Resource utilisation and economic evaluation

Health and social service resource use associated with botulinum toxin type A therapy is costed according to established methods [55-58]. Measurement and valuation of resource use is undertaken using a combination of routine administrative data and primary data collection methods devised specifically for the study. Costs measured and valued include the costs of the drugs, costs of the upper limb rehabilitation programme (e.g. staff time) and costs associated with any adverse side effects associated with the administration of the drugs (e.g. general practitioner or other health care contacts, contacts with social services, out of pocket payments by participants for pain relieving drugs). The costs of the drugs is ascertained from suppliers. Staff time is recorded and costed using gross hourly wage rates derived from the mid-point of appropriate salary scales. Costs of rehabilitation equipment e.g. upper limb splinting is obtained from routine data. The frequency of participant contacts with health professionals and social services is ascertained through the administration of a participant questionnaire at the 1, 3 and 12 month outcome assessments. Participants are asked about any contacts they have had with health care professionals and social services since their last assessment and to indicate any out of pocket expenditure they have incurred for medication. As the study period is 12 months, there is no need to apply discounting. The economic evaluation combines the cost data with data on outcomes from the Euroqol EQ-5D[28] which is used to estimate the quality adjusted life years (QALYS) gained from the intervention. An incremental cost per QALY gained for botulinum toxin plus upper limb therapy relative to therapy alone will be estimated and associated cost-effectiveness acceptability curves presented. Sensitivity analysis will be undertaken to assess the sensitivity of the results to variations in key parameters.

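### The 15% target is an absolute difference, but the only interval named is for an unstratified odds ratio, and that odds ratio is sent into a cost-per-QALY analysis that gives it no role

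*Protocol article*

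**What the plan says.** In the protocol article, Statistical analysis, each participant is classed as a success or not from the change in ARAT at one month. The proportion of successes "in each group will then be compared using Fisher's exact test". The section then adds: "An interval estimate of the relative odds of a successful outcome in each group will also be calculated". No stratification is mentioned for the test or the interval, although the Randomisation section stratifies on three ARAT bands (0–3, 4–28, 29–56). The next sentence gives the interval a use: "This interval estimate of effect size will be taken forward into the economic evaluation".

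The same section sets the target on another scale: "A clinically important treatment effect is defined as a difference in good outcomes between intervention and control groups of 15" per cent. The design assumption is that "it is expected to see 20% of the control group achieve good outcomes and 35% of the intervention group achieve good outcomes", and the sample is sized "to give us 80% power to detect a 15% difference in good outcomes".

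The section Resource utilisation and economic evaluation describes what the odds ratio is supposed to feed. "The economic evaluation combines the cost data with data on outcomes from the Euroqol EQ-5D", from which QALYs are estimated. The outputs are an incremental cost per QALY, acceptability curves, and a sensitivity analysis on key parameters that are not listed. The study period is 12 months. ARAT success is not mentioned, and no model links it to utility or cost.

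**The concern.** **Scale.** The trial was sized for an absolute difference, and readers will ask whether the result supports or excludes a difference of that size. Fisher's test gives a p-value and no estimate. An odds ratio interval answers the question only once it is combined with a control rate. That rate was uncertain at the design stage: half the sample was to come from the ARAT 0–3 group, which the amendments section says could not be predicted to improve as much. If success rates differ between bands, a pooled odds ratio also need not equal the odds ratio within each band.

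**Destination.** An analyst following the Statistical analysis section would look for a place to put a one-month ARAT odds ratio in the economic evaluation. An analyst following the economic section would never need it. The article thus leaves open whether QALYs come directly from participants' EQ-5D or are in some part driven by ARAT success. These are different analyses and can give different answers.

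**Working it through.** **Inputs.** Statistical analysis: success 20% (control) and 35% (intervention), two-sided 5%, 80% power, Fleiss' method, 10% inflation, total 332. Randomisation: 1:1. Control rates other than 20% below are illustrative assumptions; the article gives only 20%.

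**1. The article's own figure.** Mean proportion (0.20 + 0.35)/2 = 0.275.

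n′ = [1.960 × √(2 × 0.275 × 0.725) + 0.8416 × √(0.20 × 0.80 + 0.35 × 0.65)]² / 0.15² = 137.9, so 138 per arm.

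With the continuity correction: n = (n′/4) × [1 + √(1 + 4/(n′ × 0.15))]² = 151 per arm, 302 in total. Then 302 × 1.10 = 332.2. The stated 332 reproduces with the continuity correction; without it the inflated total would be about 304 to 308.

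**2. The target as an odds ratio.** (0.35/0.65)/(0.20/0.80) = 2.15.

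**3. How the two scales separate.** With control rate c and odds ratio 2.15, the intervention odds are o = 2.15 × c/(1 − c) and the difference is o/(1 + o) − c. Conversely, the odds ratio for a 15-point difference is [(c + 0.15)/(0.85 − c)]/[c/(1 − c)].

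| Control rate | Difference if odds ratio is 2.15 | Odds ratio if difference is 15 points |
|---|---|---|
| 5% | 5.2 points | 4.75 |
| 10% | 9.3 points | 3.00 |
| 20% | 15.0 points | 2.15 |
| 30% | 18.0 points | 1.91 |

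(Points here are percentage points, not ARAT points.)

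**4. What each interval would look like at the design rates, 151 evaluable per arm.**

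- Odds ratio: SE(log) = √(1/30.2 + 1/120.8 + 1/52.85 + 1/98.15) = 0.2655; 95% CI 1.28 to 3.62.
- Risk difference: SE = √[(0.16 + 0.2275)/151] = 0.0507; 95% CI 5.1 to 24.9 points.
- Converting the odds ratio limits at a fixed 20% control rate: 1.28 × 0.25 = 0.32, and 0.32/1.32 = 24.2%, a difference of 4.2 points; 3.62 × 0.25 = 0.906, and 0.906/1.906 = 47.5%, a difference of 27.5 points.

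The observed control rate therefore recovers the point difference exactly. It does not recover the interval: 4.2 to 27.5 is not 5.1 to 24.9.

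**5. Why stratify.** Take two equal halves with control rates of 10% and 30% and an odds ratio of 2.15 in each. From step 3 the intervention rates are 19.3% and 48.0%. Pooled, this is 20% against (19.3 + 48.0)/2 = 33.7%, and the crude odds ratio is (0.337/0.663)/0.25 = 2.03, although it is 2.15 in both halves. The risk difference averages directly: (9.3 + 18.0)/2 = 13.7 points, the same as the pooled difference. The gap is small in this example, but it affects only the odds ratio.

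**6. The two sections side by side.** The Statistical analysis section supplies a relative effect on ARAT success at one month. The economic section needs incremental cost and incremental QALYs over 12 months, with their joint uncertainty for the acceptability curves. It obtains QALYs from EQ-5D, which Table 1 schedules at screening and at 1, 3 and 12 months. Nothing in it takes an odds ratio as input.

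**The case against.** The strongest reply is that little is lost. Powering on a difference and reporting an odds ratio is common and is not in itself an error. The success proportions will be reported, so the difference follows by subtraction. This is a condensed article; a full list of effect measures and the detailed QALY methods belong in the analysis plan or a health-economics plan, neither of which is shown. The odds ratio might enter only the sensitivity analysis on key parameters without displacing EQ-5D. All of this stands, and it keeps the point minor. What it does not answer is that the one interval named is off the target's scale and ignores the randomisation bands, and that the carry-forward sentence is stated outright with no counterpart in the economic section.

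Three stronger readings are tempting and should be resisted.

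- A reader might infer that the primary result could not be judged against 15 percentage points at all. It could, because the control rate will be observed; only the interval is missing.
- A reader might infer that all QALY gain would be routed through one-month ARAT success, so that benefits in passive care would be lost and the acceptability curve would be wrong. The background does place the main benefits in earlier trials in global ratings and "itemised passive disability scores (notably hand hygiene"), and it does not name pain among them. But no section describes such a model, and the economic section says that EQ-5D is used to estimate the QALYs. The harm depends on a use the article does not describe.
- A reader might infer that the sample size or the test is compromised. Neither is.

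**Conclusion.** The point holds as a minor one, in two parts. The planned interval is on a different scale from the stated target and matches it only at a 20% control rate; at illustrative control rates of 5% to 30%, an odds ratio of 2.15 spans 5.2 to 18.0 percentage points. Separately, the Statistical analysis section gives the one-month ARAT odds ratio a destination that the economic section does not recognise. The first part costs interpretability, not validity. The second is an inconsistency of wording whose practical effect cannot be sized from the article. The intervals calculated here assume the design success rates and 151 evaluable participants per arm. A full protocol or analysis plan may already settle the reporting scale, but the mismatch between the two sections stands in the article as published.

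**What to change.** 1. In Statistical analysis, state that the difference in treatment success (intervention minus control) will be reported with a 95% confidence interval, stratified by the randomisation ARAT bands 0–3, 4–28 and 29–56 (for example with Mantel–Haenszel weights). Keep the odds ratio beside it, and interpret the difference and its interval against 15 percentage points. Fisher's test and the sample size stay as they are.
2. Delete the carry-forward sentence, or confine it to a named secondary or sensitivity analysis and say how the ARAT effect enters.
3. Say in the economic section that base-case QALYs and their uncertainty come from participants' EQ-5D and costs, preferably with QALYs adjusted for the EQ-5D already collected at screening.

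The cost is a few sentences and minor analysis work. No additional data, visits or participants are needed.
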